## Abstract

**Background:**

Cervical spinal cord injury (SCI) results in severe upper limb impairment, with restoration of hand and arm function ranked as the highest rehabilitation priority by individuals with tetraplegia. Transcutaneous spinal cord stimulation (tSCS) has emerged as a promising approach for enhancing upper limb recovery. Intermittent theta burst stimulation (iTBS), an efficient form of repetitive transcranial magnetic stimulation, can enhance cortical excitability and descending motor drive. However, the benefit of combining these complementary neuromodulation modalities to simultaneously target supraspinal and spinal circuits has not been evaluated in a controlled trial.

**Objective:**

This study aims to evaluate the feasibility, safety, and preliminary efficacy of combined cortical neuromodulation (iTBS) and spinal neuromodulation (tSCS) versus tSCS alone, each paired with standardized upper limb rehabilitation, for improving upper limb motor function in chronic incomplete cervical SCI.

**Methods:**

This single-center, two-arm, assessor-blinded, pilot randomized controlled trial will enroll 24 adults aged 21–65 years with chronic (more than 12 months post-injury) incomplete cervical SCI (American Spinal Injury Association Impairment Scale grade C or D, neurological level C2 to C8) at Alexandra Hospital, Singapore. Participants will be randomized 1:1 to receive either iTBS combined with tSCS plus standardized upper limb rehabilitation or tSCS plus upper limb rehabilitation alone. Interventions will be delivered twice weekly for 12 weeks (24 sessions). The primary outcome is the change in Upper Extremity Motor Score from baseline to 12 weeks. Secondary outcomes include measures of upper limb function, independence, spasticity, corticospinal excitability, quality of life, and goal attainment. Assessments will be conducted at baseline, post-intervention, and at 4- and 12-week follow-up.

**Results:**

This protocol was approved by the National Healthcare Group Domain Specific Review Board. Recruitment is expected to begin in the third quarter of 2026, with data collection anticipated to be completed by the fourth quarter of 2027.

**Conclusion:**

This pilot trial will provide the first controlled evidence on whether adjunctive cortical neuromodulation via iTBS produces additional upper limb motor recovery beyond tSCS-based rehabilitation in chronic incomplete cervical SCI. Feasibility data and effect size estimates will inform the design of a subsequent multicenter confirmatory trial.

**Clinical trial registration:**

ClinicalTrials.gov, identifier NCT07586644.

## Introduction

### Background

Spinal cord injury (SCI) is a devastating neurological condition that disrupts motor, sensory, and autonomic function, leaving millions worldwide with chronic disability. The World Health Organization estimates that SCI affects approximately 15.4 million people globally (Lu et al., 2025). Among those with cervical-level injuries, which account for roughly half of all traumatic SCI cases globally (Safdarian et al., 2023), impairment of upper extremity (UE) function profoundly limits independence in activities of daily living and quality of life (Ahuja et al., 2017; van Silfhout et al., 2017). Restoration of hand and arm function is consistently identified as the highest rehabilitation priority by individuals with tetraplegia, surpassing even recovery of locomotion and bladder control (Anderson, 2004). Despite advances in conventional rehabilitation approaches, including physical therapy, occupational therapy, and activity-based training, functional recovery of the upper limb in the chronic phase of cervical SCI remains limited, highlighting a critical unmet clinical need (James et al., 2018; Sayenko et al., 2015).

The pathophysiological basis of motor impairment in incomplete cervical SCI involves disruption of descending corticospinal and other supraspinal motor pathways, alongside reorganization of spinal interneuronal circuits below the level of injury (Anderson et al., 2022; Zholudeva et al., 2018). Critically, incomplete SCI is characterized by the preservation of residual neural pathways bridging the lesion site, representing a biological substrate for experience-dependent and stimulation-driven neuroplasticity (Hutson and Di Giovanni, 2019). It is increasingly recognized that neuroplasticity is activity-dependent, suggesting that external neuromodulatory stimuli may enhance recovery after SCI when paired with structured rehabilitation (Barss et al., 2022; Behrman et al., 2006; Dietz and Fouad, 2014; Raineteau and Schwab, 2001; Zheng et al., 2020). This understanding has catalyzed the development of novel non-invasive neurostimulation strategies targeting both cortical and spinal levels of the motor neuraxis.

### Transcutaneous spinal cord stimulation

Transcutaneous spinal cord stimulation (tSCS) is a non-invasive neuromodulation technique that delivers electrical stimulation through surface electrodes positioned over the posterior aspect of the spine. Typically employing biphasic rectangular waveforms with carrier frequencies of 5–10 kHz delivered at 30–70 Hz, tSCS activates large-to-medium diameter sensory afferent fibers in the dorsal roots, which supply excitatory synaptic connections to motoneurons and spinal interneuronal circuits (Hofstoetter et al., 2020; Sayenko et al., 2015). Seminal work by Gerasimenko et al. (2015) demonstrated that tSCS can enable voluntary movements in individuals with motor-complete SCI, providing foundational evidence for spinal circuit reactivation. Subsequent investigations have confirmed the feasibility and preliminary efficacy of tSCS for improving motor function, standing ability, and walking parameters in individuals with incomplete injuries (Hofstoetter et al., 2021; Taccola et al., 2018).

A systematic review by Tajali et al. (2024), published in Frontiers in Neuroscience in 2024, demonstrated that tSCS modulates both spinal and corticospinal excitability, with studies showing increased motor evoked potentials and decreased H-reflex amplitudes following alternating current tSCS, indicating enhanced neuroplasticity at multiple levels of the motor system.

The strongest clinical evidence for cervical tSCS comes from the Up-LIFT trial, a prospective, single-arm, multicenter study published in Nature Medicine in 2024 by Moritz et al. (2024). This trial enrolled 60 participants with chronic cervical SCI at 14 international centers and demonstrated that non-invasive spinal cord electrical stimulation (ARCEX Therapy) combined with structured rehabilitation significantly improved upper limb strength, function, and sensation compared to rehabilitation alone. The study reported that 72% of participants met the primary effectiveness endpoint, with significant improvements in fingertip pinch force, hand prehension, UE motor and sensory scores, and self-reported quality of life. No serious adverse events related to stimulation were observed. In December 2024, the ARC-EX System received FDA *de novo* authorization, marking the first FDA-cleared non-invasive spinal cord stimulation system for SCI (Mertz, 2025).

Subsequent studies have extended these findings. A home-based extension of the Up-LIFT trial, published in Neurology Clinical Practice in 2025, demonstrated that tSCS can be safely and effectively delivered in the home environment (Tefertiller et al., 2025). Programming recommendations based on analysis of stimulation parameters from both the Up-LIFT and LIFT Home trials were published in Neuromodulation in 2025, providing a clinical framework for parameter selection (Gelenitis et al., 2025). A real-world pilot study by Suggitt et al. (2025), published in Neuromodulation in 2025, confirmed the safety and effectiveness of multisite tSCS combined with activity-based therapy in a community rehabilitation setting. A comprehensive review by Singh et al. (2024) in the Journal of Neurotrauma in 2024 synthesized the evidence for cervical tSCS in UE recovery and concluded that, although the evidence base is limited in sample size, findings consistently suggest that tSCS combined with task-specific training improves voluntary control of arm and hand function. A systematic review by Wankner et al. (2026), published in Life in 2026, further synthesized preclinical and clinical evidence across epidural, intraspinal, and transcutaneous modalities and confirmed the therapeutic promise of cervical spinal cord stimulation while emphasizing the need for standardized protocols and larger controlled trials.

### Repetitive transcranial magnetic stimulation

Repetitive transcranial magnetic stimulation (rTMS) is a non-invasive brain stimulation technique that modulates cortical excitability through pulsed magnetic fields generated by a coil positioned over the scalp (Rossini et al., 2015). When applied at high frequencies or in patterned protocols over the primary motor cortex (M1), rTMS increases corticospinal excitability and has been shown to promote motor recovery in various neurological conditions. The therapeutic mechanisms are believed to involve enhancement of descending corticospinal drive, promotion of cortical reorganization, and induction of long-term potentiation (LTP)-like plasticity at cortical synapses (Fan et al., 2025).

Intermittent theta burst stimulation (iTBS) is a patterned rTMS protocol that delivers bursts of 3 magnetic pulses at 50 Hz, repeated at a theta frequency of 5 Hz, producing facilitatory after-effects on cortical excitability that last well beyond the stimulation period (Huang et al., 2005). A key practical advantage of iTBS is its brevity: a standard 600-pulse session is completed in approximately 3–4 min, compared with 10–20 min for conventional high-frequency rTMS protocols. We recognize, however, that current iTBS evidence derives predominantly from research settings rather than routine clinic use. Its short duration and portable equipment footprint make clinical translation plausible, and this pilot will prospectively capture setup time, therapist burden, and equipment turnover data to directly assess scalability in routine rehabilitation workflows, which has not yet been established.

A comprehensive review of rTMS for SCI, published in the International Journal of Molecular Sciences in January 2025, summarized the current evidence and concluded that rTMS has demonstrated therapeutic effectiveness in increasing corticospinal transmission, enhancing voluntary motor output, improving motor function, alleviating spasticity, and reducing neuropathic pain in individuals with SCI (Fan et al., 2025). The review highlighted iTBS and combined approaches as promising future directions. A feasibility study by Gharooni et al. (2018) examined iTBS for upper limb dysfunction and spasticity in SCI and demonstrated that it was safe and well tolerated, supporting its use in larger clinical trials. More recently, Feng et al. (2023) conducted a pilot randomized controlled trial of cerebral theta-burst stimulation combined with physiotherapy in patients with incomplete SCI and demonstrated significant improvements in lower limb motor scores, walking speed, stride length, and functional independence measures. Shi et al. (2026) further confirmed the efficacy of excitatory iTBS on lower limb recovery in chronic incomplete SCI. A recently published protocol in JMIR Research Protocols by Patel et al. (2025) described a five-arm randomized controlled trial of iTBS for sensorimotor recovery in complete SCI, underscoring the growing research interest in this technique for the SCI population.

### Rationale for combined stimulation: convergent neuromodulation

While both tSCS and rTMS have independently shown promise, neither modality alone addresses the full complexity of the disrupted corticospinal neuraxis in cervical SCI. rTMS enhances descending cortical drive from above the lesion, whereas tSCS increases spinal circuit excitability below the lesion. The theoretical rationale for combining these modalities is that simultaneous top-down cortical facilitation and bottom-up spinal priming may produce synergistic or supra-additive effects on motor recovery, a concept termed “convergent neuromodulation” (Benavides et al., 2020; Wang et al., 2023). Simultaneous delivery is required (not sequential) because spike-timing-dependent plasticity depends on iTBS-primed descending volleys arriving at sublesional motoneurons within ∼10 to 20 ms of tSCS-evoked afferent volleys, enabling Hebbian coincidence detection. Sequential delivery dissipates the brief iTBS after-effect window before afferent priming is engaged; standalone modalities leave either descending drive or sublesional excitability sub-threshold.

This concept is supported by several converging lines of evidence. First, paired associative stimulation (PAS) paradigms, which combine TMS with peripheral or spinal stimulation, have been shown to strengthen corticospinal connections through spike-timing-dependent plasticity (STDP) mechanisms. A systematic review of cortico-spinal PAS in SCI published in Expert Review of Medical Devices in 2024 evaluated 10 studies involving 84 patients and found that PAS improved motor outcomes (Martino Cinnera et al., 2024). Second, Pulverenti et al. (2021, 2022) conducted randomized clinical trials pairing TMS with transcutaneous transspinal stimulation during locomotor training in individuals with chronic SCI, demonstrating neurophysiological changes indicative of spinal synaptic strengthening across multiple segments. Third, the systematic review by Tajali et al. (2024) explicitly called for more rigorous studies comparing the effects of combined neuromodulation versus single techniques on functional and neural recovery after SCI. Fourth, a pilot study by Lin et al. (2023) combining rTMS with transspinal electrical stimulation in individuals with incomplete SCI demonstrated enhanced corticospinal excitability, supporting the feasibility of multi-level stimulation.

Despite this theoretical and preliminary evidence, no controlled clinical trial has evaluated the combined application of rTMS (or iTBS) and tSCS for upper limb recovery in cervical SCI. The present protocol addresses this critical evidence gap.

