### Interventions

#### Overview

Both arms will receive individualized tSCS combined with standardized upper limb rehabilitation. The experimental arm will additionally receive iTBS immediately prior to each rehabilitation session. Interventions will be delivered twice per week for 12 weeks, yielding a total of 24 sessions. A minimum of 20 completed sessions (83%) will be required for per-protocol analysis.

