#### Intermittent theta burst stimulation protocol (experimental arm only)

iTBS will be delivered before each tSCS and rehabilitation session using a figure-of-eight coil connected to a biphasic magnetic stimulator (MagPro X100 with MC-B70 figure-of-eight coil, MagVenture, Denmark, or equivalent). The coil will be positioned over the hand representation area of the primary motor cortex (M1) contralateral to the more impaired upper limb. The motor hotspot will be determined as the scalp location yielding the largest and most consistent motor evoked potentials (MEPs) in the first dorsal interosseous (FDI) or abductor pollicis brevis (APB) muscle. The active motor threshold (AMT) will be determined using the relative frequency method as the minimum stimulator intensity eliciting discernible MEPs in at least 5 of 10 consecutive trials during slight voluntary contraction (approximately 10% of maximum).

The iTBS protocol will consist of bursts of 3 magnetic pulses delivered at 50 Hz, repeated at a theta frequency of 5 Hz, with 2-s trains repeated every 10 s for 20 repetitions, delivering a total of 600 pulses per session (Huang et al., 2005). Stimulation intensity will be set at 80% of AMT. Each iTBS session will last approximately 3–4 min and will be completed before electrode placement and tSCS activation. These parameters are consistent with established international safety guidelines for rTMS (Lefaucheur et al., 2020; Rossini et al., 2015) and with the iTBS protocols employed in recent SCI studies (Feng et al., 2023; Patel et al., 2025; Shi et al., 2026).

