#### Treatment session sequence

Each session in the experimental arm will follow the sequence: (1) iTBS over M1 (approximately 3–4 min); (2) tSCS electrode placement and activation (approximately 5 min setup); (3) combined tSCS plus upper limb rehabilitation (approximately 45–60 min). Total session duration for the experimental arm is approximately 55–70 min. The control arm follows the same sequence without the iTBS component, with total session duration of approximately 50–65 min.

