We acknowledge that activity-based restorative therapy literature typically favors 3–5 sessions per week, and that the 3–4 day inter-session gaps in our protocol may attenuate the cumulative spike-timing-dependent priming effects that denser schedules could achieve. This introduces a risk of Type II error should the intervention prove effective only at higher densities. We have retained the twice-weekly schedule because (i) the total dose of 24 sessions matches the Up-LIFT trial, enabling cross-study comparison; (ii) iTBS after-effects on cortical excitability persist beyond single sessions and may partially bridge inter-session gaps; (iii) feasibility and retention are primary pilot objectives; and (iv) most participants in our outpatient setting rely on caregiver-assisted transport, making thrice-weekly attendance impractical. Session density will be explicitly re-evaluated as a design parameter for the subsequent confirmatory trial, and pilot effect-size estimates should be interpreted as a lower bound on achievable benefit. The inclusion of a 12-week post-intervention follow-up extends beyond the single 4-week follow-up used in some prior studies, providing more robust data on durability of treatment effects.

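### The rationale requires iTBS and tSCS to be simultaneous and says sequential delivery fails, but the Methods deliver them sequentially, so the results cannot bear on the simultaneous spike-timing mechanism

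*Protocol article*

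**What the plan says.** **Rationale.** The Introduction section on combined stimulation makes timing a condition: "Simultaneous delivery is required (not sequential) because spike-timing-dependent plasticity depends on iTBS-primed descending volleys arriving at sublesional motoneurons", with arrival within about "10 to 20 ms of tSCS-evoked afferent volleys, enabling Hebbian coincidence detection". It then rules out the alternative: "Sequential delivery dissipates the brief iTBS after-effect window before afferent priming is engaged".

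**Methods.** Three sections give the opposite order.
- Interventions, Overview: "The experimental arm will additionally receive iTBS immediately prior to each rehabilitation session".
- iTBS protocol: the iTBS session "will be completed before electrode placement and tSCS activation".
- Treatment session sequence: iTBS is step 1 (3–4 min), step "2) tSCS electrode placement and activation (approximately 5 min setup"), and step 3 is tSCS together with rehabilitation (45–60 min).

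**Duration of the after-effect.** The rationale calls it brief. The Introduction section on rTMS says the facilitation considerably outlasts the stimulation. The Discussion (Comparison with prior work), defending the twice-weekly schedule, says "iTBS after-effects on cortical excitability persist beyond single sessions and may partially bridge inter-session gaps".

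**Hypotheses and question.** The Hypotheses section expects at least 2 additional UEMS points and greater corticospinal plasticity with adjunctive iTBS. The primary objective and the question posed in the Discussion likewise concern the benefit of adding iTBS. None of these sets a timing condition.

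**The concern.** Read literally, the rationale says that the regimen in the Methods cannot engage the mechanism for which the two stimulations are combined. That mechanism is not incidental. The Abstract frames the evidence gap as acting on cortical and spinal circuits at the same time. The note under the eligibility table justifies the restriction to motor-incomplete injury by spike-timing plasticity. The Discussion and Conclusion interpret the trial as one of convergent neuromodulation. If the mismatch stays, results from a sequential regimen would be read as evidence on a simultaneous one, and that reading would carry into the planning of the confirmatory trial.

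**Working it through.** The point rests on comparing texts. The arithmetic only confirms that the Methods describe a truly sequential session.

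**1. Reproduce the stated iTBS dose and length.** Inputs are from the iTBS protocol: 3 pulses per burst, 5 bursts per second, "with 2-s trains repeated every 10 s for 20 repetitions, delivering a total of 600 pulses per session".
- Pulses: 2 s × 5 bursts/s × 3 pulses × 20 trains = 600, as stated.
- Duration: 19 intervals × 10 s + 2 s = 192 s = 3.2 min, within the stated 3–4 min.

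**2. Check that the stated session lengths imply sequential delivery.** Inputs are from the Treatment session sequence.
- Experimental arm, components end to end: 3 + 5 + 45 = 53 min to 4 + 5 + 60 = 69 min. Stated: about 55–70 min.
- Control arm: 5 + 45 = 50 min to 5 + 60 = 65 min. Stated: about 50–65 min.
- If iTBS ran during tSCS or during set-up, the experimental session would be no longer than the control session. The article makes it about 5 min longer, so iTBS time is added in front.

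**3. Overlap.** tSCS runs during rehabilitation, and iTBS is complete before the electrodes are placed.
- Pulses delivered with tSCS on: 0 of 600 per session; 0 of 600 × 24 = 14,400 over the course.
- Last iTBS pulse to tSCS: about 5 min. First pulse to tSCS: 192 s + 300 s = 492 s, about 8.2 min.

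**4. Set the after-effect statements side by side.**

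| Section | What it implies |
|---|---|
| Rationale for combined stimulation | Brief; lost under sequential delivery before tSCS engages |
| Repetitive transcranial magnetic stimulation | Considerably outlasts the stimulation |
| Comparison with prior work | Outlasts single sessions; may partly span gaps of 3–4 days |

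If the first row applies to this regimen, the useful window closes within the set-up time of about 5 min. The third row relies on some persistence over days. The third row is hedged, but the article offers nothing that reconciles it with the first.

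**5. What each result could show, on the rationale's own terms.**
- Null: this is what the rationale would predict if the mechanism were real but not engaged, so it cannot refute the mechanism.
- Positive: benefit would have arisen without any overlap. That says nothing on whether overlap does what the rationale claims, so it cannot support the mechanism.
- Neurophysiology: CMCT and MEP changes at weeks 12, 16 and 24 can show altered corticospinal function, but not that it arose from coincident volleys.

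**The case against.** **A softer reading of the rationale.** The primed descending volleys could be voluntary drive during later training under tSCS, with iTBS merely raising cortical excitability beforehand. The Discussion (Principal considerations) is compatible with this. It would fit the Methods, but the rationale's next sentence blocks it by saying that sequential delivery loses the after-effect before spinal priming engages.

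**The trial's question is unaffected.** This objection stands. A reader might infer that the trial cannot test its stated hypotheses. The documents do not support that: the hypotheses, the primary objective and the Discussion's question all concern adjunctive iTBS, and the arms differ by exactly that. A reader might also infer that the estimated effect belongs to some other intervention. It belongs to the one the Methods define, and the Methods sections agree with one another on the order.

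**Size.** It is tempting to divide the 5-minute gap by the 10–20 ms window. The two are unlike quantities: the window describes when volleys arrive at motoneurons, not a permitted interval between devices. Zero overlap is the relevant fact.

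**Existing caveats.** The Statistical analysis section labels all efficacy comparisons exploratory, and the Limitations concede that the independent contribution of iTBS cannot be separated from its interaction with tSCS. Both are fair, but neither addresses the timing contradiction.

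**Conclusion.** The contradiction is real, and nothing in the article resolves it. The rationale demands simultaneous delivery and rejects sequential delivery; the Methods specify sequential delivery with zero overlap and about 5 min of set-up between the two. The statements on how long the after-effect lasts also conflict, although the Discussion's claim is qualified.

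The consequence is limited. The added effect of iTBS as delivered can be estimated, within the limits of an open-label pilot of 24. What is lost is any inference about the simultaneous spike-timing mechanism, in either direction. Randomization, primary outcome, sample size, analysis and progression criteria are unaffected. The conclusion assumes only that the rationale and the session sequence mean what they say. It does not depend on the exact set-up time, because overlap is zero however short the set-up is.

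**What to change.** Before first enrolment, reconcile the Abstract (Background), the Introduction sections on rTMS and on combined stimulation, the Discussion (Principal considerations; Comparison with prior work) and the Conclusion with the Interventions overview, the iTBS protocol and the Treatment session sequence. No view is taken here on which sequence is right.

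If the Methods sequence stands:
- remove the statements that simultaneity is required and that sequential delivery fails;
- give one consistent account of how long the after-effect lasts;
- describe the comparison as adding iTBS before tSCS-based rehabilitation;
- limit mechanistic conclusions to that regimen, and state that neither a positive nor a null result bears on the simultaneous mechanism.

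The hypotheses and primary objective can stay as they are. The cost is wording only. If the sponsor instead confirms simultaneous delivery, the Methods sections and stated session lengths need a protocol amendment. The Results section reports no participants enrolled at manuscript preparation, so either route is still open without affecting collected data.
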